### **Modified Schedule of Activities**

The schedule of activities below should be followed for all post month 60 visits after January 1, 2019 for all cohorts. For the PD and Healthy Control cohorts, this may include month 72, 84, 96, 108, 120, 132, 144 and 156 visits; for the Prodromal and Genetic cohorts, this may include month 72, 84, 96, 108 and 120 visits.

#### **5.3.20 Modified annual in clinic visit**

- Review of continuing ability to consent/Advance Directive
- Consent/withdrawal of consent for contact regarding future studies related or unrelated to PPMI
- Review willingness to share contact information with FOUND or, if enrolled in FOUND, review individual status report
- PPMI Brain and Tissue Bank (for subjects who did not yet sign a form providing permission to be contacted by the Brain and Tissue Bank study team or have not yet signed an Intent to Donate form, review subject interest in PPMI Brain and Tissue Bank and remind interested subjects to follow up with the Brain and Tissue Bank study team or have subject sign an Intent to Donate form)
- Participant Questionnaire (Prodromal and Unaffected Genetic cohort subjects only; questionnaire to be completed prior to subject interacting with investigator)
- General neurological examination (Prodromal and Unaffected Genetic Cohort subjects only)
- Vital signs
- Blood draw for research samples
- Blood draw for PBMCs
- PASE Exercise Questionnaire
- Epworth Sleepiness Scale
- REM Sleep Behavior Disorder Questionnaire
- GDS-15
- State-Trait Anxiety Inventory for Adults
- Questionnaire for Impulsive-Compulsive Disorders
- SCOPA-AUT
- Montreal Cognitive Assessment (MoCA)
- Letter Number Sequencing
- Hopkins Verbal Learning Test – Revised (use next subsequent form; see PPMI Operations manual for schedule of forms)

- Symbol Digit Modalities Test (alternate form 1 and 2; see PPMI Operations manual for schedule of forms)
- Benton Judgment of Line Orientation (alternate odd and even items; see PPMI Operations manual for schedule )
- Semantic Fluency (animals only)
- Trails A and B
- Lexical Fluency (FAS)
- Boston Naming Test
- Cognitive Categorization Assessment
- Determination of Falls
- NeuroQOL
- UPSIT (at every annual visit for PD, PD Genetic Cohort and Healthy Control subjects; at V12, V14, V16, V18 and V20 for Prodromal and Unaffected Genetic Cohort subjects)
- MDS-UPDRS Parts I-III (Part IV also conducted at each visit for subjects who have started PD medication)
- Hoehn and Yahr
- Modified Schwab & England (except Healthy Control subjects)
- MDS-UPDRS Part III and Hoehn & Yahr will be repeated one hour following dosing in clinic for subjects who have started levodopa or dopamine agonist
- Review of clinical diagnosis
- Lumbar puncture for collection of CSF (V12, V14, V16, V18 and V20 only)
- DatSCAN (at one time point only and only for selected subjects in prodromal and genetic cohorts)
- Review of current medical conditions
- Review of concomitant medications
- Review of adverse events related to lumbar puncture (if lumbar puncture performed)

### **5.3.21 Telephone Contacts**

Telephone call visits will be conducted 7 to 10 days following a visit when lumbar puncture and/or dopamine transporter SPECT imaging has occurred to assess for adverse events. In addition, after Month 12, telephone call visits will take place 3 months through month 60 following each in-person visit to discuss any questions, verify whether or not PD medications have been started and to confirm the date of the next scheduled visit.

After month 60 during the Modified Schedule of Activities, telephone call visits will take place 6 months after each annual in person visit. During those visits the following activities will occur:

- Consent to share contact information for FOUND
- Consent to share contact information for PPMI Brain and Tissue Bank
- Confirmation of vital status
- Confirm/update subject contact information
- Clinical diagnosis review

- Participant Questionnaire (Prodromal and Unaffected Genetic cohort subjects only)

Refer to F-AV-133-PPMI companion protocol for telephone follow up requirements for subjects participating in VMAT-2 PET imaging and refer to [18F] florbetaben companion protocol for telephone follow up requirements related to that study.

### **5.3.22 Unscheduled Visits (Visit U01, U02, etc.), if required**

Unscheduled visits may be performed at any time during the study whenever necessary to assess for or to follow up on adverse events or as deemed necessary by the Site Investigator or Coordinator. Subjects undergoing imaging multiple assessments (e.g., subjects participating in companion imaging protocols) that require a delay between scans may complete their imaging at an unscheduled visit. Subjects consenting to skin biopsies (at participating sites) may have their biopsy completed at an unscheduled visit. Subjects consenting to an additional blood draw (at participating sites) may have their blood draw completed at an unscheduled visit. The following activities will be completed at an Unscheduled Visit:

- Review of continuing ability to consent/Advance Directive
- Review willingness to share contact information with FOUND or, if enrolled in FOUND, review individual status report
- PPMI Brain and Tissue Bank (if subject has not yet been approached regarding Brain and Tissue Bank, review subject interest in sharing contact information with PPMI Brain and Tissue Bank study team or discuss Brain and Tissue Bank and present Intent to Donate form to subject)
- Vital signs
- \*General neurological examination
- \*Collect blood for clinical laboratory assessments
- Review of current medical conditions
- Review of concomitant medications

\*Conducted only if clinically indicated

### **5.3.23 Premature Withdrawal of Participation**

If the subject agrees, the following procedures should be performed when a subject withdraws early from the study:

- Review of continuing ability to consent/Advance Directive
- Review willingness to share contact information with FOUND or, if enrolled in FOUND, review individual status report
- PPMI Brain and Tissue Bank (for subjects who did not yet sign a form providing permission to be contacted by the Brain and Tissue Bank study team or have not yet signed an Intent to Donate form, review subject interest in PPMI Brain and Tissue Bank and remind interested subjects to follow up with the Brain and Tissue Bank study team or have subject sign an Intent to Donate form)
- General neurological examination

- Height and weight
- Vital signs (blood pressure, heart rate and temperature)
- Clinical diagnosis assessment
- Review of family history of PD (Genetic Cohort only)
- Blood draw for research samples – only if not done in the last 3 months
- Urine collection for research samples – only if not done in the last 3 months
- Clinical laboratory assessments
- PASE Exercise Questionnaire
- Epworth Sleepiness Scale
- REM Sleep Behavior Disorder Questionnaire
- GDS-15
- State-Trait Anxiety Inventory
- Questionnaire for Impulsive-Compulsive Disorders
- SCOPA-AUT
- Montreal Cognitive Assessment (MoCA)
- Letter Number Sequencing
- Hopkins Verbal Learning Test – Revised (version not used at preceding visit)
- Symbol Digit Modalities Test (version not used at preceding visit)
- Benton Judgment of Line Orientation (items not used at preceding visit)
- Semantic Fluency
- Cognitive Categorization Assessment
- MDS-UPDRS Parts I-III (Part IV will also be conducted at each visit for subjects who have started PD medication)
- Hoehn and Yahr
- Modified Schwab & England (PD Prodromal, Genetic Cohort subjects only)
- MDS-UPDRS Part III and Hoehn & Yahr will be conducted again one hour following dosing in clinic for subjects who have started levodopa or dopamine agonist
- Lumbar puncture for collection of CSF – only if not done in the last 3 months
- SPECT imaging – only if not done in the last 12 months (PD, Prodromal SWEDD, and Genetic Cohort subjects only – see Section 6.3.1,) includes urine (or serum if required by site) pregnancy test for women of childbearing potential prior to injection
- VMAT-2 PET imaging – only if not done in the last 12 months for PD SWEDD, Prodromal and Genetic Cohort subjects only (refer to F-AV-133-PPMI companion protocol)
- MRI DTI and resting state (**PD**, Prodromal, SWEDD and Genetic Cohort subjects at selected sites if MRI not done in the last 12 months)
- MRI DTI and resting state (**HC** subjects at selected sites if PW visit conducted within first 12 months and MRI not done in the last 6 months)
- [F] florbetaben PET imaging if subject has not completed this imaging at earlier visit and is willing to complete at PW visit.
- Review of current medical conditions
- Review of concomitant medications

- Review of adverse events in follow up to SPECT imaging and/or lumbar puncture
- Consent/withdrawal of consent for contact regarding future studies related or unrelated to PPMI
- Lexical Fluency (FAS) [During modified schedule of activities only]
- Boston Naming Test [During modified schedule of activities only]
- Determination of falls [During modified schedule of activities only]
- NeuroQOL [During modified schedule of activities only]

### **5.3. 24 PD, SWEDD, or Prodromal Subjects Starting PD Medication:**

If the site becomes aware that a subject will begin PD medication in advance of or at the time of a scheduled visit, the site should determine if the subject is willing to conduct a Symptomatic Therapy (ST) visit prior to starting medications. If a subject is not willing to return for an ST visit prior to starting PD medication, conduct the next study visit per the regular visit schedule. If the subject agrees, an ST visit should be conducted and the appropriate visit schedule below should be followed (see Section 5.3.26 for list of ST visit assessments):

- Before Visit 01: Complete ST visit assessments. Visit 01 will be missed and the subject will return to the regular visit schedule for Visit 02.
- At Visit 01 or prior to Visit 02: Complete ST visit assessments. Visit 02 will be missed and the subject will return to the regular visit schedule for Visit 03.
- At Visit 02 or prior to Visit 03: Complete ST visit assessments. Visit 03 will be missed and the subject will return to the regular visit schedule for Visit 04.
- At Visit 03 or prior to Visit 04: Complete ST visit assessments. Visit 04 will be missed and the subject will return to the regular visit schedule for Visit 05.
- At Visit 04: Complete ST visit assessments. The subject will return to the regular visit schedule for Visit 05 assessments.
- After Visit 04: If an ST visit is conducted within 3 months prior to the next visit's Target Date, or as part of that next regularly scheduled study visit, the ST visit will replace that visit. The subject will then continue following the Visit Window Schedule. If the subject returns outside of the 3 month window prior to the next visit, conduct the ST visit. The subject will return again for the next regular study visit.

The start of PD medication should be reported to the CTCC and documented on the appropriate source worksheet.

### **5.3.25 Genetic Cohort Subjects Starting PD Medication:**

If the site becomes aware that a subject will begin PD medication in advance of or at the time of a scheduled visit, the site should determine if the subject is willing to conduct a Symptomatic Therapy (ST) visit prior to starting medications. If a subject is not willing to

return for an ST visit prior to starting PD medication, conduct the next study visit per the regular visit schedule. If the subject agrees, an ST visit should be conducted and the appropriate visit schedule below should be followed (see Section 5.3.26 for list of ST visit assessments):

- At or prior to Visit 02: Complete ST visit assessments. Visit 02 will be missed and the subject will return to the regular visit schedule for Visit 04.
- After Visit 2 but Prior to Visit 04: Complete ST visit assessments. Visit 04 will be missed and the subject will return to the regular visit schedule for Visit 05.
- At Visit 04: Complete ST visit assessments. The subject will return to the regular visit schedule for Visit 05 assessments.
- After Visit 04: If an ST visit is conducted within 3 months prior to the next visit's Target Date, or as part of that next regularly scheduled study visit, the ST visit will replace that visit. The subject will then continue following the Visit Window Schedule. If the subject returns outside of the 3 month window prior to the next visit, conduct the ST visit. The subject will return again for the next regular study visit.

The initiation of PD medication should be reported to the CTCC and documented on the appropriate source worksheet.

**5.3.26. Symptomatic Therapy Visit (PD, SWEDD, Prodromal and PD Genetic Cohort subjects only)\***

- Review of continuing ability to consent/Advance Directive
- Review willingness to share contact information with FOUND or, if enrolled in FOUND, review individual status report
- PPMI Brain and Tissue Bank (for subjects who did not yet sign a form providing permission to be contacted by the Brain and Tissue Bank study team or have not yet signed an Intent to Donate form, review subject interest in PPMI Brain and Tissue Bank and remind interested subjects to follow up with the Brain and Tissue Bank study team or have subject sign an Intent to Donate form)
- Vital signs (blood pressure, heart rate and temperature)
- Blood draw for research samples
- Urine collection for research samples
- Epworth Sleepiness Scale
- REM Sleep Behavior Disorder Questionnaire
- GDS-15
- State-Trait Anxiety Inventory
- Questionnaire for Impulsive-Compulsive Disorders
- SCOPA-AUT
- MDS-UPDRS Parts I-III
- Hoehn and Yahr
- Modified Schwab and England
- Clinical diagnosis assessment

- Review of family history of PD (PD Genetic Cohort subjects only)
- Lumbar puncture for collection of CSF (not repeated if CSF was collected less than 3 months prior to the ST visit)
- SPECT Imaging
  - ❖ Conduct for PD and Prodromal subjects when ST visit replaces a Month 12, Month 24, or Month 48 visit (as applicable)
  - ❖ Conduct for SWEDD subject when ST visit replaces Month 24 visit
  - ❖ Conduct for PD Genetic Cohort subjects when ST visit replaces a Month 12, Month 24, Month 36, or Month 48 visit (as applicable)
- VMAT-2 PET Imaging (selected sites only; refer to F-AV-133-PPMI companion protocol)
  - ❖ Conduct for PD subject when ST visit replaces Month 12, Month 24, or Month 48 visit
  - ❖ Conduct for SWEDD subject when ST visit replaces Month 24 visit
  - ❖ Conduct for PD Genetic Cohort subjects when ST visit replaces a Month 12, Month 24, Month 36, or Month 48 visit (as applicable)
- Review of current medical conditions
- Review of concomitant medications
- Review of adverse events day of visit and in follow up to lumbar puncture and/or SPECT (or VMAT-2) imaging (as applicable)
- Consent/withdrawal of consent for contact regarding future studies related or unrelated to PPMI

Additional assessments to be completed when ST visit is conducted in place of an annual visit:

- General neurological examination
- Clinical laboratory assessments
- MoCA
- Letter Number Sequencing
- Hopkins Verbal Learning Test – Revised (refer to section 6 of Operations Manual to determine appropriate form to administer)
- Symbol Digit Modalities Test
- Benton Judgment of Line Orientation
- Semantic Fluency
- Cognitive Categorization

\* Symptomatic therapy visits will not be completed as part of the modified schedule of activities.

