**5.3.8. Visit 04 (12 months  $\pm$ 30 days)**

- Review of continuing ability to consent/Advance Directive
- Review willingness to share contact information with FOUND or, if enrolled in FOUND, review individual status report
- PPMI Brain and Tissue Bank (for subjects who did not yet sign a form providing permission to be contacted by the Brain and Tissue Bank study team or have not yet signed an Intent to Donate form, review subject interest in PPMI Brain and Tissue Bank and remind interested subjects to follow up with the Brain and Tissue Bank study team or have subject sign an Intent to Donate form)
- General neurological examination
- Height and weight
- Vital signs (blood pressure, heart rate and temperature)

- Blood draw for research samples
- Urine collection for research samples
- Clinical laboratory assessments
- PASE Exercise Questionnaire
- Epworth Sleepiness Scale
- REM Sleep Behavior Disorder Questionnaire
- GDS-15
- State-Trait Anxiety Inventory
- Questionnaire for Impulsive-Compulsive Disorders
- SCOPA-AUT
- Montreal Cognitive Assessment (MoCA)
- Letter Number Sequencing
- Hopkins Verbal Learning Test – Revised (Form 2)
- Symbol Digit Modalities Test (Form 2)
- Benton Judgment of Line Orientation (Even items)
- Semantic Fluency
- Cognitive Categorization Assessment
- MDS-UPDRS Parts I-III (Part IV also conducted at each visit for subjects who have started PD medication)
- Hoehn and Yahr
- Modified Schwab & England (PD, Prodromal, SWEDD, and Genetic Cohort subjects only)
- MDS-UPDRS Part III and Hoehn & Yahr will be repeated one hour following dosing in clinic for subjects who have started levodopa or dopamine agonist
- Review of clinical diagnosis
- Review of family history of PD (Genetic Cohort subjects only)
- Lumbar puncture for collection of CSF
- SPECT imaging (PD and Prodromal subjects only – see Section 6.3.1), includes urine (or serum if required by site) pregnancy test for women of childbearing potential prior to injection
- VMAT-2 PET imaging, at selected sites, PD and Prodromal subjects (see Section 6.3.2)
- MRI-DTI and resting state (PD, Prodromal and HC subjects at selected sites)

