- [F] florbetaben PET imaging at selected sites, PD (idiopathic and genetic cohorts), Prodromal (including RBD, olfactory and genetic cohort) subjects; or may be done at either V06 (24 months), V08 (36 months), V10 (48 months) or V12 (month 60); (or at V13 (month 72), V14 (month 84) or V15 (month 96) for PD and HC cohorts); see companion protocol.
- Gait assessments, at selected sites (Genetic Cohort subjects only) (see section 6.3.9 for details)
- Review of current medical conditions
- Review of concomitant medications
- Review of adverse events in follow up to SPECT (and/or VMAT-2 PET) imaging and/or lumbar puncture

- Consent/withdrawal of consent for contact regarding future studies related or unrelated to PPMI

Note Genetic Cohort will not undergo SPECT imaging, VMAT-2 imaging or DTI at Visit 04

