**5.3.10. Visit 06 (24 months  $\pm$ 30 days)**

- Review of continuing ability to consent/Advance Directive
- Review willingness to share contact information with FOUND or, if enrolled in FOUND, review individual status report
- PPMI Brain and Tissue Bank (for subjects who did not yet sign a form providing permission to be contacted by the Brain and Tissue Bank study team or have not yet signed an Intent to Donate form, review subject interest in PPMI Brain and Tissue Bank and remind interested subjects to follow up with the Brain and Tissue Bank study team or have subject sign an Intent to Donate form)
- General neurological examination
- Height and weight
- Vital signs (blood pressure, heart rate and temperature)
- Clinical laboratory assessments

- Blood draw for research samples
- Urine collection for research samples
- PASE Exercise Questionnaire
- Epworth Sleepiness Scale
- REM Sleep Behavior Disorder Questionnaire
- GDS-15
- State-Trait Anxiety Inventory
- Questionnaire for Impulsive-Compulsive Disorders
- SCOPA-AUT
- Montreal Cognitive Assessment (MoCA)
- Letter Number Sequencing
- Hopkins Verbal Learning Test – Revised (Form 3)
- Symbol Digit Modalities Test (Form 1)
- Benton Judgment of Line Orientation (Odd items)
- Semantic Fluency
- Cognitive Categorization Assessment
- MDS-UPDRS Parts I-III (Part IV also conducted at each visit for subjects who have started PD medication)
- Hoehn and Yahr
- Modified Schwab & England (PD, Prodromal, SWEDD and Genetic Cohort subjects only)
- MDS-UPDRS Part III and Hoehn & Yahr will be repeated one hour following dosing in clinic for subjects who have started levodopa or dopamine agonist
- Review of clinical diagnosis
- Review of family history of PD (Genetic Cohort subjects only)
- Lumbar puncture for collection of CSF
- SPECT imaging (PD, Prodromal, SWEDD, and Genetic Cohort subjects only – see Section 6.3.1), includes urine (or serum if required by site) pregnancy test for women of childbearing potential prior to injection
- VMAT-2 PET imaging, at selected sites, PD, SWEDD, Prodromal and Genetic Cohort subjects only (see Section 6.3.2)
- [F] florbetaben PET imaging at selected sites, PD (idiopathic and genetic cohorts), HC, and Prodromal (including RBD, olfactory and genetic cohort) subjects if not done at V04 (12 months); or may be done at V08 (36 months), V10 (48 months) or V12 (60 months); (or at V13 (month 72), V14 (month 84) or V15 (month 96) for PD and HC cohorts); see companion protocol.

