**5.3.12. Visit 08 (36 months  $\pm$ 30 days)**

- Review of continuing ability to consent/Advance Directive
- Review willingness to share contact information with FOUND or, if enrolled in FOUND, review individual status report
- PPMI Brain and Tissue Bank (for subjects who did not yet sign a form providing permission to be contacted by the Brain and Tissue Bank study team or have not yet signed an Intent to Donate form, review subject interest in PPMI Brain and Tissue Bank and remind interested subjects to follow up with the Brain and Tissue Bank study team or have subject sign an Intent to Donate form)
- General neurological examination

- Height and weight
- Vital signs (blood pressure, heart rate and temperature)
- Clinical laboratory assessments
- Blood draw for research samples
- Urine collection for research samples
- PASE Exercise Questionnaire
- Epworth Sleepiness Scale
- REM Sleep Behavior Disorder Questionnaire
- GDS-15
- State-Trait Anxiety Inventory
- Questionnaire for Impulsive-Compulsive Disorders
- SCOPA-AUT
- Montreal Cognitive Assessment (MoCA)
- Letter Number Sequencing
- Hopkins Verbal Learning Test – Revised (Form 4)
- Symbol Digit Modalities Test (Form 2)
- Benton Judgment of Line Orientation (Even items)
- Semantic Fluency
- Cognitive Categorization Assessment
- UPSIT (Prodromal and Unaffected Genetic Cohort subjects only; if subject has already completed their month 36 visit at time of amendment 12 approval, this may be completed at a later visit)
- MDS-UPDRS Parts I-III (Part IV also conducted at each visit for subjects who have started PD medication)
- Hoehn and Yahr
- Modified Schwab & England (PD, Prodromal, and Genetic Cohort subjects only)
- MDS-UPDRS Part III and Hoehn & Yahr will be repeated one hour following dosing in clinic for subjects who have started levodopa or dopamine agonist
- SPECT imaging (Prodromal subjects only), includes urine (or serum if required by site) pregnancy test for women of childbearing potential prior to injection
- [F] florbetaben PET imaging at selected sites, PD (idiopathic and genetic cohorts), HC, and Prodromal (including RBD, olfactory and genetic cohort) subjects if not done at V04 or V06; or may be done at V10 (48 months) or V12 (60 months); (or at V13 (month 72), V4 (month 84) or V15 (month 96) for PD and HC cohorts); see companion protocol.
- MRI-DTI and resting state, HC at selected sites if not obtained at a previous visit

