**5.3.14. Visit 10 (48 months  $\pm$ 30 days)**

- Review of continuing ability to consent/Advance Directive
- Review willingness to share contact information with FOUND or, if enrolled in FOUND, review individual status report
- PPMI Brain and Tissue Bank (for subjects who did not yet sign a form providing permission to be contacted by the Brain and Tissue Bank study team or have not yet signed an Intent to Donate form, review subject interest in PPMI Brain and Tissue Bank and remind interested subjects to follow up with the Brain and Tissue Bank study team or have subject sign an Intent to Donate form)
- General neurological examination
- Height and weight
- Vital signs (blood pressure, heart rate and temperature)
- Clinical laboratory assessments
- Blood draw for research samples
- Urine collection for research samples
- PASE Exercise Questionnaire

- Epworth Sleepiness Scale
- REM Sleep Behavior Disorder Questionnaire
- GDS-15
- State-Trait Anxiety Inventory
- Questionnaire for Impulsive-Compulsive Disorders
- SCOPA-AUT
- Montreal Cognitive Assessment (MoCA)
- Letter Number Sequencing
- Hopkins Verbal Learning Test – Revised (Form 5)
- Symbol Digit Modalities Test (Form 1)
- Benton Judgment of Line Orientation (Odd items)
- Semantic Fluency
- Cognitive Categorization Assessment
- MDS-UPDRS Parts I-III (Part IV also conducted at each visit for subjects who have started PD medication)
- Hoehn and Yahr
- Modified Schwab & England (PD, Prodromal, and Genetic Cohort subjects only)
- MDS-UPDRS Part III and Hoehn & Yahr will be repeated one hour following dosing in clinic for subjects who have started levodopa or dopamine agonist
- Review of clinical diagnosis
- Review of family history of PD (Genetic Cohort subjects only)
- Lumbar puncture for collection of CSF
- SPECT imaging (PD, prodromal and Genetic Cohort subjects only – see Section 6.3.1), includes urine (or serum if required by site) pregnancy test for women of childbearing potential prior to injection
- VMAT-2 PET imaging, at selected sites, PD, and Genetic Cohort subjects only (see Section 6.3.2)
- MRI DTI and resting state (PD, and Genetic Cohort subjects at selected sites; HC at selected sites if resting state sequences were not obtained at a previous visit)

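### Section 5.3.26 (Symptomatic Therapy visit) lists imaging months that contradict the Prodromal and PD Genetic Cohort schedules; the effect is small and easy to correct

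*Protocol*

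**What the plan says.** Section 5.3.26 covers PD, SWEDD, Prodromal and PD Genetic subjects and sets the imaging for an ST visit that replaces a scheduled one.

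- SPECT, PD and Prodromal: "Conduct for PD and Prodromal subjects when ST visit replaces a Month 12, Month 24, or Month 48 visit (as applicable".
- SPECT, and in the same words VMAT-2, PD Genetic: "Conduct for PD Genetic Cohort subjects when ST visit replaces a Month 12, Month 24, Month 36, or Month 48 visit (as applicable".
- VMAT-2, other cohorts: PD at Months 12, 24 and 48, and SWEDD at Month 24. There is no Prodromal line.

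The visit sections say otherwise.

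- Month 36 (5.3.12): "SPECT imaging (Prodromal subjects only), includes urine". No VMAT-2 is listed at this visit.
- Month 12 (5.3.8): "VMAT-2 PET imaging, at selected sites, PD and Prodromal subjects (see Section 6.3.2", and then "Note Genetic Cohort will not undergo SPECT imaging, VMAT-2 imaging or DTI at Visit 04".
- Month 24 (5.3.10): "VMAT-2 PET imaging, at selected sites, PD, SWEDD, Prodromal and Genetic Cohort subjects only (see Section 6.3.2".
- Month 48 (5.3.14): "VMAT-2 PET imaging, at selected sites, PD, and Genetic Cohort subjects only (see Section 6.3.2".

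Sections 5.3.24 and 5.3.25 send sites to 5.3.26 for the ST assessments. For the Genetic Cohort, 5.3.25 states: "After Visit 2 but Prior to Visit 04: Complete ST visit assessments. Visit 04 will be missed".

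**The concern.** A site running an ST visit has two imaging rules for that visit, and they disagree. Because the ST visit replaces the scheduled one, a scan left off the 5.3.26 list is not picked up elsewhere in the regular sequence. A month wrongly on the list can prompt a radiotracer injection that the subject's own schedule does not contain. At stake are a planned Prodromal DAT scan timed before medication starts, Prodromal VMAT-2 at participating sites, and unnecessary tracer exposure in PD Genetic subjects.

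The cross-reference that should settle the conflict does not work. Footnote k, which qualifies the ST-column scans in the schedules, cites section 5.3.20. That number now belongs to the modified annual visit, which contains no ST rule.

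**Working it through.** **Comparison of follow-up imaging months.** The schedule column combines the cohort table with sections 5.3.8, 5.3.10, 5.3.12 and 5.3.14.

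| Cohort and modality | Schedule | 5.3.26 | Difference |
|---|---|---|---|
| PD, SPECT and VMAT-2 | 12, 24, 48 | 12, 24, 48 | none |
| SWEDD, SPECT and VMAT-2 | 24 | 24 | none |
| Prodromal, SPECT | 12, 24, 36, 48 | 12, 24, 48 | 36 missing |
| Prodromal, VMAT-2 | 12, 24 | no line | both missing |
| PD Genetic, SPECT and VMAT-2 | 24, 48 | 12, 24, 36, 48 | 12 and 36 extra |

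The Prodromal table marks DAT and VMAT-2 in its ST column, so neither omission follows from the schedule. Section 6.3.2 and the premature-withdrawal list in 5.3.23 also include Prodromal subjects for VMAT-2. The PD Genetic months in 5.3.26 are exactly the Prodromal SPECT months, which suggests a list attached to the wrong cohort. That is an inference.

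**Prodromal subjects affected at Month 36.** Inputs: 30% phenoconversion over 24 months (14.5); about 100 subjects; after Visit 04 an ST visit replaces the next visit if held within 3 months before its target date (5.3.24), so the window is months 33 to 36. Assumptions: constant hazard, medication start at conversion, every subject accepts the ST visit, no dropout.

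- Hazard = −ln(0.70)/2 = 0.178 per year.
- S(33 months) − S(36 months) = 0.612 − 0.586 = 0.0267, or 2.7 per 100.
- At an assumed two-year conversion of 15%: 0.0161, or 1.6 per 100. At 40%: 0.0306, or 3.1 per 100.

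These are gross figures. Section 5.3.27 calls for a phenoconversion visit, with DAT imaging, within 45 days of the site learning of the diagnosis. That visit supersedes an annual visit due within the following 2 months. Of the 0.0267, 0.0177 falls in months 34 to 36, where this applies, and 0.0090 in months 33 to 34. DAT scans still missing = 2.67 × (1 − completion of the phenoconversion visit), with completion assumed:

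- 100%: 0
- 90%: 0.27 per 100
- 75%: 0.67 per 100

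These figures exclude subjects who start medication without a diagnosis. The protocol gives nothing from which to estimate them.

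**PD Genetic subjects exposed to an extra scan.** The window is months 6 to 12 for Month 12 (5.3.25) and months 33 to 36 for Month 36. With annual start rate p, the fraction still untreated at t years is (1 − p)^t. Per 10 subjects untreated at baseline, all accepting the ST visit:

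| Assumed annual start | Replaces Month 12: 10 × [(1−p)^0.5 − (1−p)] | Replaces Month 36: 10 × [(1−p)^2.75 − (1−p)^3] |
|---|---|---|
| 30% | 1.37 | 0.32 |
| 50% | 2.07 | 0.24 |
| 70% | 2.48 | 0.09 |

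The number untreated at baseline is not given. Section 7.1.1 expects most PD Genetic subjects to be on medication by then.

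**The case against.** The strongest counter-argument concerns the PD Genetic lines. Both carry the qualifier (as applicable), section 5.3.8 expressly bars this cohort from imaging at Visit 04, and the table shows only Months 24 and 48. A site reading all three together could well skip the extra scans. This stands in part: the wording is not a firm instruction to inject. But the line covers one cohort for which Months 12 and 36 never apply, so naming those months can only mislead. The qualifier also cannot restore a month or cohort that is absent, so it does not help the Prodromal omissions.

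It could be argued that the extra PD Genetic months were deliberate, since the ST visit exists to capture data before treatment and the withdrawal visit allows SPECT off schedule. No text says so, and the bar in 5.3.8 points the other way.

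For VMAT-2, sections 5.2 and 5.3.26 refer sites to the AV-133 companion protocol. Footnote r also lets U.S. subjects take their first VMAT-2 scan at Year 1. Both points stand: whether any VMAT-2 scan would be lost cannot be judged here, and Month 12 may be legitimate for some PD Genetic subjects as an initial scan.

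The numbers are small and rest largely on assumptions. That also stands. The 2.7 ceiling treats all 100 Prodromal subjects as still ahead of Month 36, whereas 5.3.12 provides for some who had already passed it.

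**Conclusion.** The three contradictions are real, and each is shown by both the schedule table and the visit text. The PD and SWEDD entries are consistent.

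The consequence is small. For Prodromal DAT at Month 36 the gross ceiling is 2.7 per 100, and the net loss is 0 to 0.7 per 100 under the assumptions above. The main cost is timing: the replacement scan may come after medication has started. The VMAT-2 loss is not quantified. For PD Genetic subjects, about 1.4 to 2.5 per 10 untreated at baseline could have an ST visit replacing Month 12, and 0.1 to 0.3 replacing Month 36, with an unknown but probably small number untreated.

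The two-year phenoconversion estimate and the analyses of short-term change are unaffected. ST visits are not held under the modified schedule, so exposure is confined to the original one. The correction should still be made, because sites are sent to this section for the ST assessments and the error changes which scans are done.

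**What to change.** Amend section 5.3.26 to read:

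- **SPECT:** PD Months 12, 24, 48; Prodromal Months 12, 24, 36, 48; SWEDD Month 24; PD Genetic Months 24, 48.
- **VMAT-2:** PD Months 12, 24, 48; Prodromal Months 12, 24; SWEDD Month 24; PD Genetic Months 24, 48.

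Before finalising the VMAT-2 lines, check them against the AV-133 companion protocol, including whether Month 12 should stay for U.S. subjects whose first scan is deferred to Year 1. If the extra PD Genetic months were intended, the protocol should say so and reconcile them with 5.3.8 and the table.

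Change footnote k to cite 5.3.26 in place of 5.3.20; it appears under six schedule tables. Footnote g has the same fault and can be corrected together with it: it cites 5.3.18, now Visit 14, while unscheduled visits are in 5.3.22.

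The cost is a few lines of text, the footnote references, one check against the companion protocol and a notice to sites. The Prodromal scans restored are ones the schedule already plans, and the PD Genetic change removes scans.
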